## Hypotheses/aims and benefits

The aim of the current RCT is to examine whether high-intensity exercise may reduce symptoms of anxiety in patients in mental health care.

We hypothesise that:The participants performing high-intensity exercise will have a significantly larger reduction in anxiety levels compared to the participants performing low-intensity exercise.The participants performing high intensity exercise will have a significantly higher degree of compliance (meaning that they will be able to complete the training autonomously three months after participating in the project) compared to the participants performing low intensity exercise.The participants performing high-intensity exercise will have a significantly larger improvement (i.e. reduction) in blood pressure than the participants performing low-intensity exercise.

The expected benefits for the participants are positive health effects, in terms of improved physical fitness and reduced psychological symptoms. Moreover, the participants will learn to use physical activity as a specific measure that they can utilise as a source of coping. Furthermore, knowledge about physical activity and mental health may be applicable in mental health care as part of a treatment plan.

## Methods/design

This is a study protocol for a randomised controlled trial designed to test the effects of high intensity training compared to low intensity training on anxiety levels.

There will be a random 1:1 allocation into two groups. The two groups are high intensity exercise (1 × 4 minutes performed two times per week with a heart rate of 85–95% of maximal heart rate, corresponding to ≥ 16 on the 6–20 Borg scale) and low intensity exercise (45 minutes performed two times per week with a heart rate of approximately 60% of maximal heart rate, corresponding to 9–11 on the 6–20 Borg scale) [26]. The high intensity group will perform a 10-minute warm-up prior to the high-intensity bout, and a 5-minute cooldown. Due to the low intensity in the low intensity group, a warm-up is not considered necessary.

The total amount of training sessions for both groups will be eight. The high intensity exercise group will serve as the intervention group, while the low intensity exercise group will serve as an active control group.

The trial will be conducted in accordance with the Standard Protocol Items: Recommendations for Interventional Trials statement (SPIRIT) [27].

The trial has been approved by the Data Protection Officer at the University Hospital of North Norway and the Regional Committee on Health Research Ethics (approval number 714458) and registered at ClinicalTrials.gov (Trial registration number NCT06881758).

Participants will provide written informed consent before allocation to the two intervention groups, and they will be randomised into a high-intensity training group and a low-intensity training group, following baseline measures.

Randomisation will be performed using counterbalanced block randomisation in a 1:1 ratio, stratified by sex, to ensure an equal distribution of males and females across the study groups. Block sizes of four–six participants will be used. This will allow for a balanced representation of both genders in each condition. Randomisation will be conducted using a computer-generated random number sequence via the website https://www.randomizer.org/.

Outcomes will be measured immediately after inclusion (baseline), right after the very last exercise session, four weeks after the last exercise session (primary endpoint) and three months after the termination of the intervention period (secondary endpoint) (Fig. 1).

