## Abstract

**Background:**

This protocol was developed to describe the design of a randomised controlled trial that will examine the clinical efficacy of a 4-week comparison of high-intensity vs. low-intensity physical training for people suffering from anxiety. The hypothesis is that the high-intensity group will have greater benefit in terms of reduced anxiety symptoms, improved physical health (blood pressure) and better adherence.

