A recent meta-analysis concluded that performing endurance exercise at a high intensity may also reduce anxiety and depression [16]. High intensity exercise is shorter in duration (often shorter than 30 minutes) and with a heart rate between 85%–95% of maximal heart rate [17]. High intensity exercise is often performed in interval form, consisting of intermittent bouts of high and low intensity, a method which has been used frequently in research in recent years.

A so-called “4 × 4” interval session consisting of four minutes of high intensity divided into four bouts is a popular way of performing high-intensity exercise [18]. Recent studies have however found that the difference between performing 1 × 4 (i.e. one bout of four minutes) and 4 × 4 is small and non-significant in terms of training effect, measured by maximal oxygen uptake [19].

However, there has been some uncertainty regarding whether high-intensity exercise is superior to low-intensity exercise for mental health benefits [20]. A previous study found high-intensity exercise to have a significantly better effect on anxiety, compared to exercising at a lower intensity [21].

A more recent review by Singh and colleagues [14] also found high intensity exercise to have a better effect on mental health than lower intensity exercise. Additionally, the anxiety-suppressant and anti-depressant effect of high intensity exercise may come about rapidly, often after days or weeks [14]. An assumed mechanism is a larger secretion of signalling substances (serotonin and norepinephrine) following high intensity exercise compared to low intensity exercise [22]. Thus, it is important to examine the effect of high intensity exercise on mental health and whether a 1 × 4-interval protocol may be recommended for patients in mental health care.

An advantage of high intensity exercise is the shorter time required to complete a session compared to low intensity exercise. A high intensity exercise session is often completed in 20–30 minutes, with two sessions per week being sufficient. Thus, high intensity exercise is a time-efficient way of exercising, shown to have a higher compliance than exercising at lower intensities [23].

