#### Change in blood pressure

Blood pressure will be measured as a secondary outcome, reflecting physiological stress response and cardiovascular health. As the link between blood pressure and anxiety remains underexplored, this study may provide novel insights into this relationship.

Participants’ changes in blood pressure, i.e. any difference between blood pressure measured at inclusion and at the end of the 4-week intervention, will be a secondary outcome measure.

Blood pressure at baseline is also part of the medical screening to exclude participants with very high blood pressure not compatible with exercise participation.

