#### Adherence

Adherence will be assessed by the number of completed sessions and heart-rate data compliance. The training schedule is flexible, allowing participants to make up missed sessions in subsequent weeks to support adherence.

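### The visits t1 and t2 are timed from each participant's last training session, while make-up sessions have no stated end, so time from randomisation to assessment can depend on adherence, which the plan expects to differ by arm

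*Protocol article*

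**What the plan says.** **Visit timing.** Methods/design sets the post-baseline visits at "right after the very last exercise session, four weeks after the last exercise session (primary endpoint"), followed by one "three months after the termination of the intervention period (secondary endpoint"). The legend of Table 1 repeats this for t1, t2 and t3. Thus t1 and t2 are tied to the last session, and t3 to the end of the intervention period. No section counts a visit from randomisation or baseline.

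**Make-up sessions.** Under Adherence: "The training schedule is flexible, allowing participants to make up missed sessions in subsequent weeks to support adherence". No latest date is given.

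**Four-week wording.** Intervention group and Comparison group each describe a 4-week programme of eight sessions, two a week. The abstract places an evaluation after 4 weeks of intervention. Change in blood pressure defines its outcome as "any difference between blood pressure measured at inclusion and at the end of the 4-week intervention".

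**Expected adherence by arm.** The abstract's hypothesis is that "the high-intensity group will have greater benefit in terms of reduced anxiety symptoms, improved physical health (blood pressure) and better adherence". The background describes high-intensity exercise as "shown to have a higher compliance than exercising at lower intensities". The measure is defined under Adherence: "Adherence will be assessed by the number of completed sessions and heart-rate data compliance".

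**The concern.** Randomisation makes the arms comparable at a given time after allocation. If the visit date is set by when a participant finishes or abandons training, it is set by behaviour that follows allocation. If that behaviour differs by arm, the arms are measured at different elapsed times, and any change in anxiety over that interval enters the group contrast. Statistical analysis names the post-tests as immediate, four-week and three-month measurements. As printed, it describes no adjustment for the elapsed time behind those labels.

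There is a second problem for participants who stop early. A visit directly after the last session can be held only if someone knows at the time that the session is the last. For a participant who simply does not return, that moment has passed before anyone knows. The visit is then likely to be missing because of poor adherence. The plan expects about 20% attrition, which is 6 of 30 participants (0.20 × 30).

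**Working it through.** **1. The plan's own figure.** Inputs from Sample size calculation: post-treatment BAI 14 versus 22 (difference 8), SD 7, two-sided alpha 0.05, power 80%.

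- n per arm = 2 × (1.96 + 0.84)² × 7² / 8² ≈ 12.02. The plan states 12 per arm, 24 in total.
- Power at 12 per arm = Φ(8 / (7 × √(2/12)) − 1.96) = Φ(2.80 − 1.96) = 0.80. The exact t-test gives 0.76.
- 24 / (1 − 0.20) = 30, as stated.

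The planned contrast of 8 points is therefore the yardstick. The sample size itself is not in question here.

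**2. How far visits can move** (taking training to start at randomisation).

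- Four sessions missed and made up at two a week after week 4: 4 / 2 = 2 extra weeks, so t1 is at week 6 and t2 at week 10. This is an extreme case.
- Stopping after session 3: last session at about week 1.5, t2 at about week 1.5 + 4 = 5.5, and no workable t1.

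**3. Possible gap between arms.** The document gives no attendance rates, so these are assumptions: two slots a week, each attended with the same probability, every missed session added at the end, no limit, and weeks counted whole. Simulated mean time to the eighth session:

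| Attendance per slot | Mean weeks to last session |
|---|---|
| 100% | 4.0 |
| 90% | 4.6 |
| 80% | 5.2 |
| 70% | 6.0 |

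Attendance of 90% versus 80% gives a gap of about 0.6 week; 90% versus 70% gives about 1.3 weeks. The gaps would be smaller if some sessions were made up inside the four weeks.

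**4. What a gap does to the contrast.** Shift = weekly change × gap in weeks. The document gives no time course. The largest rate it suggests is the expected control-arm fall from 30 to 22 spread evenly over four weeks: (30 − 22) / 4 = 2 points a week. The low end, 0.25, is assumed.

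| Gap between arms | Shift at 0.25 points/week | Shift at 2 points/week |
|---|---|---|
| 0.5 week | 0.125 | 1 |
| 1 week | 0.25 | 2 |
| 2 weeks | 0.5 | 4 |

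For one week: 0.25 / 8 = 3% and 2 / 8 = 25%. If the low-intensity arm is the one measured later and scores are still falling, the contrast shrinks to between 7.75 and 6. Power at 12 per arm (same formula) then falls from 0.80 to between 0.77 and 0.56.

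**5. Direction.** Make-up sessions delay t1 and t2, while early stopping brings t2 forward. Poor adherence in one arm can produce both, so the net direction is not determined.

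**The case against.** The strongest case on the other side has five parts.

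- **Make-up sessions may fit inside the four weeks.** The Adherence text refers to later weeks without saying after week 4, and an extra session in week 3 or 4 satisfies every section. This stands in part: spill-over is not inevitable. But no limit is stated, and sessions missed late can only be made up after week 4.
- **The expected difference between arms is thinly supported.** A reader might cite the compliance hypothesis under Hypotheses/aims and benefits. That hypothesis concerns training autonomously three months after the project, which comes after t1 and t2 and cannot move them, so it is not support. The abstract's hypothesis and the background remark remain, and the abstract's term is adherence, which the protocol measures by completed sessions.
- **Timing from the last session is a legitimate choice.** It equalises time since training, which suits the stated interest in residual effects. This stands, and it makes the matter a design choice with a cost rather than an error. The choice still gives no workable t1 for early stoppers.
- **Missing data are provided for.** Mixed models use all available observations, multiple imputation is a sensitivity analysis, and t2 remains definable for early stoppers. True, but neither method corrects visits held at different elapsed times, and both rest on data missing at random, which adherence-related loss makes harder to defend.
- **An article condenses.** Visit windows may be in the full protocol, so their absence is not the point. The point is the last-session rule that the article states, alongside an open make-up rule and 4-week wording that do not fit together.

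**Conclusion.** The concern holds for t1 and for t2, the visit labelled the primary endpoint. It applies to participants whose make-up sessions run past week 4 and to those who stop early. It should be corrected, but it is not a fatal flaw.

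Three stronger readings are not supported:

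- **That every visit is affected.** t3 is tied to the end of the intervention period and moves only if make-up sessions extend that period, which the text leaves open.
- **That a quarter of the planned effect is at risk.** The 25% needs both a one-week gap between arms and a change of 2 points a week. The gap is assumed. The rate is an upper end, taken from the expected result of a training programme rather than from drift over calendar time. The range for a one-week gap is 3% to 25%.
- **That the trial is biased towards high intensity.** If the low-intensity arm is simply measured later while scores fall, the bias runs against high intensity, and early stopping can pull the other way. Neither direction nor size can be found from the document.

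**What to change.** Schedule t1, t2 and t3 at fixed times from randomisation, identical in both arms and with stated windows: t1 at the end of the planned four weeks, t2 four weeks later, and t3 at the corresponding date. Assess everyone on those dates, including early stoppers, whatever number of sessions was completed. Record the date of each participant's last session. Recruitment began in January 2025, so for participants already assessed under the present rule, examine elapsed time from randomisation in a sensitivity analysis.

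Reconcile the make-up rule under Adherence with the 4-week wording in the abstract, Intervention group, Comparison group and Change in blood pressure. How make-up sessions should be handled is for the investigators; the visit dates should simply not depend on it.

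The cost is wording in the protocol and Table 1, with no change to the sample size. The real downside is that a participant still making up sessions is assessed at t1 before finishing, and t2 then falls less than four weeks after the last session. Someone finishing in week 6, for example, would have t2 at week 8, two weeks after training. The recorded last-session date lets this be described.

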**ASSESSMENTS:**					
***Demograpichs***	X	X			
***MINI***		X			
***BAI***		X	X	X	X
***HADS***		X	X	X	X
***Blood pressure***		X	X	X	X
***EKG***		X	X	X	X

*MINI* Mini International Neuropsychiatric Interview [28], *BAI* Beck Anxiety Inventory [24], *HADS* Hospital Anxiety and Depression Scale [25], *EKG* electrocardiogram

t_1_ = right after the very last exercise session

t_2_ = four weeks after the last exercise session

t_3_ = three months after the termination of the intervention period

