## Study setting

The study will take place at the Division of Substance Use and Mental Health at the University Hospital of North Norway, UNN-Åsgård, [name], Norway.

The study participants will be examined by medical staff (doctors) to assess eligibility for participation in the study. The screening will include a clinical interview where the MINI-interview will be used [28]. The following descriptive characteristics will be collected: sex, age, body weight, height, waist circumference, blood pressure, pulse, respiratory frequency, temperature, somatic and psychiatric diagnoses and current medication.

Furthermore, a medical examination will be performed in order to ensure the patient can handle the physical training. In addition, a resting state EKG will be taken, a blood sample will be drawn, and the following analyses will be performed: haemoglobin, haematocrit, HbA1c, electrolytes, liver function tests, kidney function tests, TSH and fT4, lipids and PRO-BNP.

Following inclusion in the study, a study nurse will assist the participants in performing the psychometric tests.

At the study Hospital, there are two separate rooms for physical training, fitted with treadmills and other equipment for physical training. The interventions (physical training) will be carried out with the supervision of an exercise physiologist.

The treadmills are of the type Lexco T560 (Lexco, South Korea) and the patients will also be fitted with heart monitor belts of the type Polar H10 (Polar Electro, Finland).

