## Outcomes

### Primary outcome measures

The primary outcome measure will be the degree of anxiety symptoms measured by the Hospital Anxiety and Depression Scale (HADS) [25] and the Beck Anxiety Inventory (BAI) [24] prior to the first (pre) and after the last (post) training session is completed.

The HADS is a questionnaire that measures self-report levels of some symptoms of anxiety and depression [25]. The instrument consists of 14 questions (items), of which 7 are related to anxiety symptoms (HADS-A) and 7 to depression symptoms (HADS-D). Each item is rated from 0 to 3, which gives a range of scoring from 0 to 42, with a score ranging between 0 and 21 for the anxiety (HADS-A) and depression (HADS-D) subscales. The HADS is one of the most commonly used self-report instruments for measuring anxiety and depression [29] and has demonstrated good reliability and validity and has sound psychometric properties [29]. A previous study found a minimal clinically important difference (MCID) between 0.5 and 5.57 for the HADS-D, and between 0.81 and 5.21 for HADS-A [30]. We will calculate total HADS scores and subscores for anxiety symptoms and depressive symptoms, respectively.

The Beck Anxiety Inventory (BAI) [24] is a questionnaire that measures self-report levels of some symptoms of anxiety. The instrument consists of 21 questions (items), and each item is rated from 0 to 3, which gives a range of scoring from 0 to 63, a higher score indicating increased symptoms. The BAI measures anxiety symptoms including muscle tension, dizziness, racing heart, nervousness, fear of dying, abdominal discomfort, face flushing, sweating, light-headedness, fear of the worst happening and a feeling of choking. The BAI is one of the most commonly used self-report instruments for measuring anxiety [31] and has demonstrated good reliability and validity and has sound psychometric properties [32]. We will calculate total BAI scores.

Both the Hospital Anxiety and Depression Scale (HADS) and the Beck Anxiety Inventory (BAI) will be applied. HADS allows comparability with both psychiatric and somatic populations, while BAI provides a more detailed assessment of somatic anxiety symptoms. Using both HADS and BAI increases sensitivity and also validity in assessing anxiety.

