#### Heart rate variability

Heart rate variability (HRV), derived from ECG recordings, will be applied as a physiological indicator of autonomic regulation and stress response. HRV provides an objective complement to the self-reported anxiety measures (HADS and BAI), which measure the participants’ subjective experience of anxiety symptoms.

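### The first post-test (t1) directly follows an exercise bout that differs by arm, so its arm difference mixes acute exertion with training adaptation, chiefly for blood pressure and HRV

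*Protocol article*

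**What the plan says.** Three places in the protocol article fix the timing of t1 in the same sense. Methods/design lists the post-tests as "right after the very last exercise session, four weeks after the last exercise session (primary endpoint", followed by a visit at three months. The Table 1 footnote reads "t_1_ = right after the very last exercise session". The statistical analysis section describes the first of the three post-tests as immediate and analyses change from baseline to it.

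Table 1 marks BAI, HADS, blood pressure and EKG at baseline, t1, t2 and t3. The EKG also supplies a further outcome: "Heart rate variability (HRV), derived from ECG recordings, will be applied as a physiological indicator of autonomic regulation and stress response".

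The preceding session is not the same in the two arms. High intensity is "1 × 4 minutes performed two times per week with a heart rate of 85–95% of maximal heart rate", with a 10-minute warm-up and a 5-minute cooldown. Low intensity is 45 minutes at about 60% of maximal heart rate.

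Baseline is taken on inclusion, before any training. In Study setting, the screening examination specifies that "a resting state EKG will be taken". No rest period, resting condition or separate visit is given for t1.

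The blood-pressure outcome is defined as "any difference between blood pressure measured at inclusion and at the end of the 4-week intervention".

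**The concern.** The trial asks whether four weeks of training at one intensity changes anxiety and physiology more than training at another. A reading taken straight after a session also picks up the body's short-term response to that session, and that response depends on intensity, the factor being randomised. Randomisation balances what participants bring to the trial. It does not balance what they did minutes before the measurement. Adjusting for age or baseline HADS-D does not help either.

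The protocol's own reasoning points this way. The Background expects more release of signalling substances after high- than after low-intensity exercise. It attributes the hoped-for blood-pressure benefit to cardiovascular and autonomic adaptation. The third hypothesis concerns that adaptation, but at t1 it would be tested on post-exercise readings. HRV, offered as an objective complement to self-report, would be recorded during recovery from two different loads.

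For BAI the route is symptom content: "The BAI measures anxiety symptoms including muscle tension, dizziness, racing heart, nervousness, fear of dying, abdominal discomfort, face flushing, sweating, light-headedness". Several of these can also be felt after exertion.

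**Working it through.** **1. Conditions at each measurement, side by side**

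| | Baseline | t1, high intensity | t1, low intensity | t2, both arms |
|---|---|---|---|---|
| Preceding activity | no training session described | 4 min at 85–95% of maximal heart rate, then 5 min cooldown | 45 min at about 60% | four weeks since last session |
| Rest condition stated | resting EKG at screening | none | none | none |

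Write the t1 arm difference in change from baseline as T + A. T is the difference in training adaptation and A the difference in acute response. Baseline carries no acute term, so subtracting it leaves A in place. At t2, A is absent.

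**2. Which outcomes rest on t1**

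- Blood pressure: of the four visits in Table 1, t1 best matches the end of the four-week intervention. This is an inference; the outcome section does not name t1.
- HRV: no single visit is named. The statistical analysis section uses EKG change at all three post-tests, so t1 is one of three.
- BAI: Methods/design gives the primary-endpoint label to t2. The Abstract points to the end of the four weeks, and the outcome section compares before the first session with after the last. On those two descriptions t1 would be primary.

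**3. The plan's own sample size**

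Inputs from the sample size section: expected BAI 14 versus 22, so a difference of 8; SD 7; two-sided alpha 0.05; power 80%; 12 per arm.

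- Normal approximation: n = 2 × (1.960 + 0.842)² × 7² / 8² = 12.02 per arm, close to the stated 12 (13 if rounded up).
- Attrition: 24 / 0.8 = 30, as stated.
- Exact t calculation at 12 per arm: power 76.3%.

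**4. How much an acute term would matter (assumed range)**

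The documents give no value for A, so let a between-arm acute shift of b points be added. With 12 per arm the standard error is 7 × √(2/12) = 2.86, with 22 degrees of freedom. The noncentrality is b / 2.86 with no training effect, and (8 ± b) / 2.86 with the planned one.

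| b (BAI points) | b in SD units (b/7) | Significant t1 difference, no training effect | Power for 8 points, shift opposes | Power for 8 points, shift adds |
|---|---|---|---|---|
| 0 | 0 | 5.0% | 76.3% | 76.3% |
| 1 | 0.14 | 6.3% | 64.9% | 85.3% |
| 2 | 0.29 | 10.3% | 51.9% | 91.7% |
| 3 | 0.43 | 17.1% | 38.7% | 95.7% |
| 4 | 0.57 | 26.8% | 26.7% | 98.0% |

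The no-effect column depends only on b/SD. It therefore applies equally to blood pressure or HRV compared by a two-sample t-test with 12 per arm. The protocol gives no SD or planned difference for those outcomes, so the power columns cannot be carried over.

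**The case against.** The strongest reply has five parts.

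- **The labelled primary visit is t2.** This is correct, and t2 is free of acute exertion. A reader might infer that the trial's main result is biased. The documents do not support that as it stands: it would follow only if the Abstract and the outcome section govern, and that conflict needs reconciling in its own right. Even then the symptom argument concerns BAI; no comparable argument is made for HADS, the other primary measure.
- **The high-intensity arm cools down for 5 minutes.** This stands and probably narrows the contrast. It does not remove it, since the other arm has just finished 45 minutes of exercise.
- **Rest, posture and time of day before a reading belong in the full protocol.** This is fair for measurement detail, and the full protocol may contain a rest rule. But the concern is not an omission. The article states three times that t1 is taken directly after the session.
- **BAI may ask about a longer period than the moment of completion.** The article gives no recall period, so this stands, and the BAI effect is less certain than that on blood pressure or HRV.
- **Size and sign are unknown.** This stands. A reader might count the exertion-like symptoms, assign a point to each and set the sum against the planned 8 points. Nothing in the documents supports such a figure, and the shift could also go the other way.

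**Conclusion.** The concern holds. As written, the t1 arm difference in blood pressure and HRV combines training adaptation with an acute response that differs by arm. The consequence is clearest for blood pressure, where a named hypothesis would be tested on readings that do not isolate adaptation. BAI as a primary outcome is affected only if t1 turns out to be the primary visit. The t2 and t3 comparisons are not affected.

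The size is unknown. The only quantitative statement available is conditional: in a trial this small, an acute shift of about 0.3 to 0.6 SD would raise the chance of a spurious t1 finding from 5% to roughly 10–27%. An opposing shift of 2 to 4 BAI points would cut power for the planned effect from 76.3% to between 51.9% and 26.7%. These figures rest on an assumed shift, the plan's SD of 7, 12 completers per arm and a simple two-sample comparison, not the repeated-measures model.

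The conclusion also assumes that t1 is measured as the article says, without an unstated rest period long enough for the acute response to pass.

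**What to change.** **Remaining participants.** Move the t1 assessment to a non-exercise day within a few days of the last session. Use the same resting conditions and time of day as baseline, identically in both arms, and reword Methods/design, Table 1 and the statistical analysis section to match.

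**Participants already assessed straight after exercise.** Describe their t1 data as including acute response, flag the assessment regime in the analysis, and report the t2 comparison alongside t1 as the one free of acute exertion. Where clock times were logged, report the interval since the end of the session.

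**Timing of the decision.** Name the visit for the blood-pressure and HRV comparisons, and settle which visit is primary for BAI and HADS, before outcome data are compared by arm.

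**Cost.** One short visit is moved. Recruitment began in January 2025 and was due to finish in March 2026, so t1 will mix two assessment regimes in about 30 participants; if few remain, most t1 data keep the acute component. Using t2 alone needs no new visit but is not a free substitute, because it reflects four weeks without supervised training and so answers a question about persistence.
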